### Recruitment {15}

Recruitment will be supported by providing study site investigators with clear enrollment targets, regular performance feedback, and educational materials for potential participants. Engagement activities such as investigator meetings and outreach within clinical networks will promote awareness and enrollment adequacy.

## Assignment of interventions: allocation

### Sequence generation {16a}

Participants will be randomized in a 1:1 ratio with random block sizes to either the investigational or comparator group, with site-specific randomization lists to ensure balanced allocation.

### Concealment mechanism {16b}

Randomization will be implemented using a secure, validated electronic data capture system with concealed allocation sequences. The randomization code will not be accessible to investigators until allocation, preventing selection bias.

### Implementation {16c}

The randomization will be implemented via the electronic data capture system secuTrial^®^ system to ensure allocation concealment. The system restricts access to the allocation sequence until the point of randomization, ensuring that the investigator is not aware of group assignment in advance. Randomization of eligible patients will be requested by the investigator after preoperative examination and timely before the planned date of surgery.

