### Eligibility criteria {10}

#### Inclusion criteria

Participants eligible for inclusion in the study are male and female patients aged 18 years or older who have provided written informed consent prior to participation. Eligible participants must have been diagnosed with a periprosthetic joint infection (PJI) according to the European Bone and Joint Infection Society (EBJIS) criteria [11], with the infection classified as chronic based on the recommendations of the Pro-Implant Foundation (PIF, Berlin, Germany) [12]. These patients must be indicated for unilateral, cementless acetabular and hip stem revision surgery due to chronic periprosthetic infection, which may involve either a single-stage or two-stage surgical procedure, as determined by the clinical standards of the investigation site. Additionally, participants must be assessed by the clinical investigator as therapy compliant and capable of attending all follow-up visits required by the study protocol. Finally, only patients with an American Society of Anesthesiologists (ASA) physical status classification of I to III prior to explantation of the infected prosthesis will be included in the study [13].

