### Intervention description {11a}

The intervention is the implantation of a permanent implant. A revision will only be performed if necessary due to medical reasons. Both investigational and comparator devices will be implanted during a single surgical procedure performed as part of a one-stage or two-stage revision hip arthroplasty, depending on the clinical indication and surgeon’s preference. All patients will undergo the same preoperative preparation, intraoperative protocols, and postoperative follow-up procedures, ensuring consistency across the two groups. Follow-up visits will be conducted according to the study protocol, with data collected on infection rates, functional and radiological outcomes, pain levels, and safety parameters at predefined time points.

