### Relevant concomitant care permitted or prohibited during the trial {11d}

Participants will receive concomitant care and medications based on clinical standards applicable to the treatment of PJI. No specific prohibitions on concurrent therapies unrelated to infection management exist.

Following completion of the trial, participants will be treated according to the standard of care practice of the treating surgeon.

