## Assignment of interventions: blinding

### Who will be blinded {17a}

The participants will be blinded to the intervention group they are allocated to, while the surgeons performing the procedures cannot be blinded due to visible differences in the investigational and comparator devices. Radiological analyses will also be conducted in a blinded manner through central radiology analysis.

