### Methods for additional analyses (e.g., subgroup analyses) {20b}

Subgroup analyses will explore outcomes stratified by patient factors such as surgical treatment (one-stage vs. two-stage revision), infection severity, and baseline functional status. Adjusted analyses may be conducted using multivariable regression models to account for potential confounders (e.g., age, comorbidities, and ASA physical status).

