However, several limitations must be acknowledged. First, the single-blinded design means that surgeons are aware of the implant type being used, which could introduce performance bias. While the use of the objective EBJIS criteria mitigates this risk, subtle differences in surgical handling or postoperative management could theoretically influence outcomes. Second, the study’s follow-up period of 12 months is sufficient to capture early postoperative infections but may not fully assess long-term implant performance and infection prevention. Longer-term follow-up studies will be necessary to confirm sustained benefits of the antimicrobial coating beyond 2 years postoperatively. Another potential limitation is the variability in surgical techniques and institutional infection control protocols across different study sites, which could influence outcomes. Additionally, the study is conducted in different countries with different microbial spectra and resistances, which could further impact the results. While the study attempts to standardize surgical and postoperative protocols, inherent differences between surgeons and institutions remain a potential source of heterogeneity.

If the study confirms a significant reduction in PJI rates with IP-coated implants, future research should focus on long-term outcomes, including implant survival, functional performance, and patient-reported quality of life. Additional studies should also evaluate the cost-effectiveness of this technology, considering the potential reduction in infection-related hospitalizations, reoperations, and antibiotic use. Moreover, exploring the applicability of this infection-preventive strategy to other orthopedic implants, such as knee or shoulder revisions, could further broaden its clinical impact.

Conversely, if the study fails to demonstrate a significant reduction in infection rates, further investigations will be needed to refine the antimicrobial coating technology or explore alternative strategies for infection prevention. Understanding the reasons behind potential treatment failure—whether related to coating durability, bacterial resistance, or host factors—will be crucial in guiding future innovation in orthopedic biomaterials.

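### The arm can be known before surgery while articulation and, mainly for planned one-stage patients, staging may still change, and no step is described that fixes these choices before allocation is shown

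*Protocol article*

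**What the plan says.** On timing, Implementation {16c} reads: "Randomization of eligible patients will be requested by the investigator after preoperative examination and timely before the planned date of surgery". In Table 1 the randomisation row is marked in the pre-surgical column headed -7 to -2. Participant timeline {13} identifies the surgery visit as implantation of the study device. Concealment mechanism {16b} adds: "The randomization code will not be accessible to investigators until allocation, preventing selection bias".

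On blinding, Who will be blinded {17a} says that "the surgeons performing the procedures cannot be blinded due to visible differences in the investigational and comparator devices".

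On what the surgeon may choose:
- Explanation for the choice of comparators {6b} leaves articulation, including a dual mobility option, to patient and surgical factors.
- The inclusion criteria describe revision surgery "which may involve either a single-stage or two-stage surgical procedure, as determined by the clinical standards of the investigation site". Intervention description {11a} instead makes staging depend on clinical indication and on what the surgeon prefers.
- Concomitant care {11d} says: "Participants will receive concomitant care and medications based on clinical standards applicable to the treatment of PJI".

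As safeguards, Intervention description {11a} states: "All patients will undergo the same preoperative preparation, intraoperative protocols, and postoperative follow-up procedures, ensuring consistency across the two groups". The Discussion admits possible performance bias and continues: "While the use of the objective EBJIS criteria mitigates this risk, subtle differences in surgical handling or postoperative management could theoretically influence outcomes".

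On subgroups, section {20b} says: "Subgroup analyses will explore outcomes stratified by patient factors such as surgical treatment (one-stage vs. two-stage revision), infection severity, and baseline functional status".

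**The concern.** The reason given for not blinding surgeons is that the two devices look different. That reason applies only once the implant is in view. It does not require the arm to be known during planning. Withholding the code until allocation prevents selective enrolment, but that protection ends when the allocation is shown, which by Table 1 is before the operation.

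If a choice made after that point differs by arm and affects reinfection, the comparison estimates coating plus co-treatment. Such a difference could favour either arm. More intensive care of controls would shrink the contrast, and more intensive care of coated patients could mimic superiority. Neither the intention-to-treat nor the per-protocol analysis would remove it.

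The mitigation offered in the Discussion does not reach this. Objective criteria limit biased assessment of the outcome. If co-treatment changes the true reinfection rate, the EBJIS criteria record the changed rate correctly.

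The one-stage versus two-stage subgroup has a related weakness. It is listed as a patient factor, yet for a patient planned for one stage the procedure performed could change after the arm is known.

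**Working it through.** **1. What is known when.** Request for randomisation: after the preoperative examination and before surgery ({16c}, Table 1). Code accessible: from allocation ({16b}). Implant opened: at 0. Between allocation and 0 the article describes no restriction on who knows the arm, and no entry that fixes the surgical plan beforehand. Randomisation lists are by site only ({16a}), so staging is not balanced by design.

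**2. What may still change.** Articulation is open by {6b}. Staging is only partly open. The abstract includes patients already planned for one or two stages. Because 0 is implantation of the study device, a two-stage patient randomised within the week before it would normally have been explanted already. The staging concern is therefore mainly about planned one-stage patients.

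**3. The plan's own figure.** Inputs from Sample size {14}: 21.5% versus 8.6%, one-sided α = 0.025, 120 per arm. With pooled variance under the null and no continuity correction,

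power = Φ{[Δ√n − 1.96·√(2p̄(1−p̄))] / √(p₁(1−p₁) + p₂(1−p₂))}.

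Here Δ = 0.129, p̄ = 0.1505 and √120 = 10.954. The numerator is 1.413 − 0.991 = 0.422, the denominator is √(0.1688 + 0.0786) = 0.497, and Φ(0.848) = 80.2%. The stated 240 patients at 80% power reproduce.

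**4. Illustration.** The relative co-treatment effects below are assumptions; the documents give none. The same formula is used with one arm's rate multiplied by the assumed relative risk. The 180-per-arm columns correspond to the 360 evaluable patients at the maximum extension and treat that size as fixed.

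*Coating without effect (21.5% in both arms), co-treatment lowers risk in the coated arm only: chance of a false superiority claim*

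| Relative risk | 120 per arm | 180 per arm |
|---|---|---|
| 1.00 | 2.5% | 2.5% |
| 0.95 | 4.0% | 4.4% |
| 0.90 | 6.1% | 7.3% |
| 0.80 | 13.2% | 17.7% |

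For 0.90 at 120 per arm: 0.215 versus 0.1935, Δ = 0.0215, p̄ = 0.20425. The numerator is 0.236 − 1.117 = −0.882, the denominator is 0.570, and Φ(−1.547) = 6.1%.

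*Coating works as planned, co-treatment lowers risk in the control arm only: power*

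| Relative risk | 120 per arm | 180 per arm |
|---|---|---|
| 1.00 | 80.2% | 93.2% |
| 0.95 | 74.2% | 89.3% |
| 0.90 | 67.3% | 84.0% |
| 0.80 | 51.1% | 68.4% |

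For 0.90 at 120 per arm: 0.1935 versus 0.086, Δ = 0.1075, p̄ = 0.13975. The numerator is 1.178 − 0.961 = 0.217, the denominator is 0.484, and Φ(0.447) = 67.3%.

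The primary analysis combines stagewise log-rank tests. The two-proportion test is used here because the plan sizes the trial with it.

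**The case against.** The strongest reply is that the plan already handles much of this. Intervention description {11a} promises the same preparation and intraoperative protocols in both groups. Variation between sites is balanced by site-specific lists. The Discussion concedes residual performance bias. Outcomes {12} foresees evaluation of surgery-related data and antibiotic therapy details, and {20b} allows adjusted analyses. Most of that is true, and surgeon discretion is not evidence of a difference by arm. But the Discussion says only that the study attempts to standardise protocols, and the adjustment factors named in {20b} are baseline characteristics. Data collected afterwards can show a departure from plan only if the plan was recorded first.

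A second reply concerns size. The assumed shifts cover any arm-dependent co-treatment, including care after the implant is seen, which no release time removes. The share due to early release is not estimated. The extension would also restore part of the lost power, though it would not reduce the false-positive risk. All of this stands, so the figures show sensitivity and do not measure this defect.

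A reader might infer that debridement and local antimicrobials are left open to a surgeon who knows the arm. The documents do not support that. This condensed article never mentions local antimicrobials and sets no rule on debridement; the full protocol may cover both. Nor does it say that the investigator who requests randomisation is the operating surgeon, although that is likely.

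**Conclusion.** The point holds as an avoidable weakness, not as a demonstrated bias. Allocation can be known before surgery by staff who are not blinded, articulation and (mainly for planned one-stage patients) staging may still change, and no described step fixes them first. The Discussion's claim that the EBJIS criteria mitigate performance bias is wrong in kind, because they limit assessment bias.

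Direction and size cannot be determined from the documents. Under the plan's rates and an assumed 10% relative effect in one arm, the one-sided error would rise from 2.5% to about 6%, or power would fall from 80% to about 67% (from about 93% to about 84% at 180 per arm). The reading of -7 to -2 as days is an inference from the neighbouring columns.

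A reader might go further and conclude that allocation concealment is broken, or that staging is open for every patient. Neither follows. The code is withheld until allocation, and staging is largely set at eligibility.

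**What to change.** 1. Enable the randomisation step in the EDC system only after planned staging, articulation and antibiotic plan have been entered in the eCRF.
2. Define the one-stage versus two-stage subgroup in {20b} by that pre-randomisation entry, not by the procedure performed.
3. Tabulate departures from the recorded plan by arm.
4. Correct the Discussion: the EBJIS criteria limit outcome-assessment bias and do not mitigate performance bias.

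The cost is a few eCRF fields, a system check and an amendment. Sample size and α do not change, and no extra patients or staff are needed. The first patient was treated on 25 June 2025, so patients already randomised will not have this entry; an early change covers more of the trial.

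Showing the allocation as close to implantation as implant logistics allow is optional. Release in the operating room would need both coated and uncoated component ranges at hand for every operation, and the documents do not show whether that is feasible at the 10 sites. Under either option, bias arising after the implant is seen remains. The change concerns recording and the timing of disclosure only; no clinical rule is proposed.

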## Assignment of interventions: blinding

### Who will be blinded {17a}

The participants will be blinded to the intervention group they are allocated to, while the surgeons performing the procedures cannot be blinded due to visible differences in the investigational and comparator devices. Radiological analyses will also be conducted in a blinded manner through central radiology analysis.

### Procedure for unblinding if needed {17b}

The study is designed to remain blinded for the participants until the closure of the database and determination of the analysis populations.

## Data collection and management

### Plans for assessment and collection of outcomes {18a}

The assessment and collection of outcomes in this clinical investigation will follow a structured approach to ensure data quality and reliability. Data will be collected using electronic case report forms (eCRFs), ensuring compliance with GDPR regulations.

### Plans to promote participant retention and complete follow-up {18b}

Retention will be promoted by flexible scheduling of follow-up visits, appointment reminders via telephone or electronic communication, and providing participants with direct contact points for study-related support or questions. Missed visits will be promptly rescheduled to minimize data loss.

### Data management {19}

When a patient agrees to participate in the clinical investigation and has signed the informed consent form, the study team at the investigation site will allocate a unique code, the subject identification (ID), to the patient. Relevant personal data, health data, and procedural information necessary to conduct the clinical investigation will be collected under this subject ID. Information to be reported to the sponsor is recorded in an eCRF. Data management including creation of eCRFs including data plausibility check, data validation, data cleaning and query procedure, medical coding, and handling of the database will be performed according to designated SOPs. A data management plan (DMP) was prepared before the start of the clinical investigation.

### Confidentiality {27}

All data will be collected in compliance with the General Data Protection Regulation (GDPR) and other applicable laws. Identifiable information is pseudonymized, with only the investigators having access to re-identification keys. Data shared with the sponsor or external parties is limited to de-identified datasets. Participants are informed of data handling, storage, and potential access by authorized personnel during the informed consent process.

### Plans for collection, laboratory evaluation, and storage of biological specimens for genetic or molecular analysis in this trial/future use {33}

The collected biological specimens will not be used for genetic or molecular analysis, nor are they intended for future ancillary studies beyond the scope of this trial.

## Statistical methods

### Statistical methods for primary and secondary outcomes {20a}

The primary endpoint of this study is the comparison of infection-free survival rates (periprosthetic infections) within 12 months after revision total hip arthroplasty (THA) due to periprosthetic joint infection. The following hypothesis will be tested:H₀ (null hypothesis): hT ≥ hCHₐ (alternative hypothesis): hT < hC

where hT represents the hazard function in the treatment group and hC represents the hazard function in the control group for the 12-month postoperative period.

The primary null hypothesis is tested using a one-tailed inverse normal combination test at *α* = 0.025, allowing for a two-stage adaptive study design that combines log-rank tests for each stage. The null hypothesis is rejected if the combined *p* < 0.025. The *p*-values for each stage (*p*₁ and *p*₂) will be calculated using a one-sided log-rank test for periprosthetic reinfections (as defined by EBJIS criteria) within 12 months post-treatment. Kaplan–Meier survival curves will be right-censored at 12 months.

Descriptive statistics or comparative analyses between the treatment and control groups for demographic data, safety, and performance variables will be conducted where appropriate. Functional outcome and quality of life in the treatment groups between treatment arms will be evaluated using a linear regression model with repeated measures. Two-year implant survival will be evaluated according to the Kaplan-Meier method and compared in the treatment arms with log-rank test for the events periprosthetic joint infections, septic revisions, and all-cause revisions. Occurrence of any radiolucent line, and occurrence of hip stem migration > 2 mm will be analyzed by using a logistic regression model with repeated measures, as well as the mean migration in patients with relevant migration (> 2 mm) by using a linear regression model with repeated measures. Safety outcomes of adverse events, device failure, and component revision between treatment arms will be evaluated by using a logistic regression.

All analyses will be based on the eligible randomized patient population. A CONSORT diagram will be used to visualize the number of participants screened, randomized, treated, and analyzed for the primary outcome. Secondary analyses will be exploratory. Secondary analyses will be performed without confirmatory character:Functional outcome and quality of life in the treatment groups between treatment arms will be evaluated using a linear regression model with repeated measures.Two-year implant survival will be evaluated according to the Kaplan-Meier [6] method and compared in the treatment arms with log-rank test for the events. ◦ Periprosthetic joint infections as defined for the primary endpoint◦ Septic revisions◦ All-cause revisionsRadiological outcome in the treatment groups for the endpoints◦ Implant migration▪ Occurrence of hip stem migration > 2 mm by using a logistic regression model with repeated measures▪ Radiological signs of loosening▪ Mean migration in patients with relevant migration (> 2 mm) by using a linear regression model with repeated measures ◦ Radiologic changes in the fixation area▪ Occurrence of any radiolucency by using a logistic regression model with repeated measures Safety outcomes of adverse events, device failure, and component revision between treatment arms will be evaluated by using a logistic regression.

Silver ion concentrations in peripheral blood and drainage fluid will be descriptively analyzed.

Results of statistical tests are evaluated using a *p*-value. The significance level is set to 5% two-sided and 2.5% one-sided, respectively. Two-sided 95% confidence intervals may be given in addition.

SAS VIYA 4 statistical software (SAS Institute Inc., Cary, NC, USA) or an adequately suited alternative will be used to generate the analysis datasets and to perform statistical calculations. The R package rpact from CRAN is used to calculate the combination of tests for primary analysis.

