### Outcomes {12}

The primary endpoint is the infection-free survival rate, evaluated to demonstrate that revision hip implants with the antimicrobial silver coating significantly reduce the rate of periprosthetic reinfections within 12 months after hip revision arthroplasty. The primary variable is the occurrence of periprosthetic joint infection classified as “infection likely” or “infection confirmed” according to the European Bone and Joint Infection Society (EBJIS) criteria [11]. The time point for assessing this outcome is 12 months postoperatively, as the silver coating is designed to provide efficacy within this period. 

Secondary endpoints will be functional outcomes assessed using the Harris Hip Score (HHS) [14], focusing on pre- and postoperative scores to determine improvements in hip functionality, as well as quality of life evaluated through the EQ-5D-5L questionnaire [15]. Further, Kaplan-Meier implant survival will be determined for endpoints including septic revisions and all-cause revisions. Radiological outcome (hip stem migration, radiological signs of loosening, radiologic observations in the fixation area) will be evaluated using standardized X-rays. Safety outcomes including device failure, signs of systemic or local argyria, and (S)AEs and (S)ADEs will be documented. In addition, specific laboratory parameters related to liver (ALT, AST, GGT) and kidney (eGFR) function, as well as inflammatory markers (e.g., CRP, leukocytes), silver ion in peripheral blood and drainage liquid, and surgery-related data, including bone defect classification, length of stay, and antibiotic therapy details will be evaluated.

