### Participant timeline {13}

The clinical investigation covers eight study-related visits (Fig. 1): one preoperative visit, the surgery itself (implantation of the investigational or comparator device), and six postoperative (p.o.) visits. All visits are within the frame of clinical standard visits. An overview of the schedule of enrollment, interventions, and assessments is shown in Table 1.

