**Fig. 1 Fig1:**
[figure not shown]
Planned study visits

**Table 1 Tab1:** Participant timeline: schedule of enrollment, interventions, and assessments

		Post-randomization			Follow-Up			
Timepoint	*−**7 to **−**2*	0	*1 to 3 days*	*2 weeks*	*6 weeks*	*6 months*	*12** months*	*24** months*
Enrollment								
Eligibility screen	X							
Informed consent	X							
Randomization	X							
Intervention/comparator								
*IP-coated device*		X						
*Non-IP-coated device*		X						
Assessments								
*Infection-free implant survival rate (signs of required revision)*			X	X	X	X	X	X
*Harris-Hip-Score, Eq-5D-5L*	X		X	X	X	X	X	X
*Radiological outcome (hip stem migration, signs of loosening, fixation) *via* X-rays*		X		X			X	X
*Safety (laboratory blood parameter, signs of systemic or local argyria, (S)AEs/(S)ADE, device failure)*			X	X	X	X	X	X

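### Table 1 schedules no pre-operative safety laboratory, and the stated HHS/EQ-5D model gives the pre-operative score no role

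*Protocol article*

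**What the plan says.** **Laboratory.** Outcomes {12} includes among the secondary variables "specific laboratory parameters related to liver (ALT, AST, GGT) and kidney (eGFR) function, as well as inflammatory markers", along with silver in blood and drainage fluid. Table 1, under Participant timeline {13}, puts the laboratory in one safety row, which covers "laboratory blood parameter, signs of systemic or local argyria", adverse events and device failure. That row is marked at 1 to 3 days, 2 weeks, 6 weeks, 6, 12 and 24 months. It has no mark at the day -7 to -2 visit or on day 0. The same section says of the schedule: "All visits are within the frame of clinical standard visits".

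**Function and quality of life.** The Table 1 row "Harris-Hip-Score, Eq-5D-5L" is marked at the day -7 to -2 visit and at all six postoperative visits. Outcomes {12} describes the HHS endpoint as "focusing on pre- and postoperative scores to determine improvements in hip functionality". Statistical methods {20a} gives the analysis, twice in the same words, as "Functional outcome and quality of life in the treatment groups between treatment arms will be evaluated using a linear regression model with repeated measures". Methods for additional analyses {20b} uses baseline functional status as a subgroup factor. It also permits adjusted analyses, giving age, comorbidities and ASA status as examples.

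**The concern.** These are two separate gaps with a common theme, the use of pre-operative information.

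The laboratory gap is one of data collection. Device safety is an aim of the trial under Objectives {7}. Patients enter with a chronic infection, and the first scheduled value falls within three days of major surgery. Without an earlier value, a raised GGT or CRP, or a low eGFR, could be new or could have been there before. No analysis plan can supply a value that was not recorded.

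The HHS/EQ-5D gap is one of model specification. The score is collected and the HHS endpoint is framed as improvement, but the model sentence does not say how the pre-operative score enters. Some choices cost precision. One choice, treating it as an outcome visit under a single averaged arm term, would pull the arm estimate towards zero, because treatment cannot affect a score taken before surgery.

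**Working it through.** **1. Schedule, row by row (Table 1)**

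| Row | Day -7 to -2 | Day 0 | 1–3 days | 2 wk | 6 wk | 6 mo | 12 mo | 24 mo |
|---|---|---|---|---|---|---|---|---|
| HHS, EQ-5D-5L | X | – | X | X | X | X | X | X |
| Safety, incl. laboratory | – | – | X | X | X | X | X | X |

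The table does show pre-operative assessments where they are planned. For the laboratory it shows none, so as scheduled the quantity (postoperative value minus pre-operative value) is undefined for every listed parameter.

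**2. Reference sample size**

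The point rests on no stated figure, but the trial's 120 per arm is used below, so it is checked first. Inputs from Sample size {14}: 21.5% and 8.6%, one-sided α = 0.025, power 80%. The mean rate is 0.1505.

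n per arm = [1.96·√(2·0.1505·0.8495) + 0.8416·√(0.215·0.785 + 0.086·0.914)]² / 0.129² = (0.991 + 0.419)² / 0.01664 ≈ 119.4, rounded up to 120.

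With 10% dropout, 120/0.9 = 133.3, rounded up to 134 per arm, or 268 in total. Both figures reproduce.

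**3. Gain from conditioning on baseline HHS/EQ-5D**

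Let r be the correlation between the pre-operative score and the score at a follow-up visit. The document gives no r, so 0.2 to 0.7 is assumed, with equal SDs and 120 per arm. Variances are relative to an unadjusted comparison of postoperative scores.

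- Baseline as covariate: 1 − r².
- Change score: 2(1 − r).
- Detectable difference (two-sided 5%, 80% power), unadjusted: (1.96 + 0.8416)·√(2/120) = 0.362 SD. With the covariate, multiply by √(1 − r²).

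| r (assumed) | Covariate, relative variance | Change score, relative variance | Detectable difference with covariate (SD) | Equivalent n per arm, 120/(1 − r²) |
|---|---|---|---|---|
| 0.2 | 0.96 | 1.60 | 0.354 | 125 |
| 0.3 | 0.91 | 1.40 | 0.345 | 132 |
| 0.5 | 0.75 | 1.00 | 0.313 | 160 |
| 0.7 | 0.51 | 0.60 | 0.258 | 235 |

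For r from 0.3 to 0.5 the variance falls by 9% to 25%. Below r = 0.5 a plain change score is less precise than ignoring baseline altogether, so the form in which baseline enters matters.

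**4. Dilution, if baseline were averaged in**

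There are seven HHS/EQ-5D time points, one pre-operative and six postoperative. Suppose all seven are outcomes, weighted equally, with one arm term and a constant postoperative effect δ. The arm estimate is then (1·0 + 6·δ)/7 = 0.857δ, a loss of about 14%. With arm-by-visit terms, or with baseline means constrained equal between arms, this loss does not arise.

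**The case against.** **On HHS/EQ-5D.** The strongest reply is that the model sentence is silent and does not exclude baseline. A repeated-measures model can carry the pre-operative score as a covariate or as a constrained response, and an article may leave that detail to the analysis plan, which is not shown. The focus of Outcomes {12} on scores before and after surgery suggests that baseline is meant to be used. This stands. A reader might infer from the model sentence that pre-operative values are left out of the arm comparisons, but silence does not show that. The dilution in step 4 is likewise conditional on a model that nothing in the document states. What remains is that the sentence as written allows choices that fit the endpoint poorly.

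**On the laboratory.** Table 1 is condensed. Its safety row pools laboratory values with events that are naturally postoperative, and several items in Outcomes {12}, such as drainage-fluid silver and antibiotic details, have no entry. A reader might infer that no pre-operative laboratory value exists at all. The table does not support that: it shows only that none is scheduled there, and routine values may well be on file. For silver, prior silver-coated devices are excluded and the comparator arm gives a reference. Blood silver is also only described: "Silver ion concentrations in peripheral blood and drainage fluid will be descriptively analyzed". The randomised control arm means that group comparisons remain interpretable without a baseline; it is the reading of individual abnormalities that suffers.

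**On part A.** It is tempting to add that the early safety decision on 20 patients is weakened. Interim analyses {21b} limits the first interim analysis to adverse events and excludes other variables, so no laboratory arm comparison is planned there. Nor do the arm models named in {20a} include a laboratory value, so no precision gain is claimed for laboratory values.

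**Conclusion.** The point holds in a limited form. As scheduled in Table 1, the safety laboratory has no pre-operative reference, so neither change from baseline nor shift tables can be produced for the liver, kidney and inflammatory parameters that the article says will be evaluated. This is the firmer half, because it concerns data capture and not analysis wording. The conclusion is about the published schedule; the full plan may hold a pre-operative sample that the pooled row does not show.

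The HHS/EQ-5D half is a lack of specification and not an error. Conditioning on a score already collected would cut the variance of the arm difference by 9% (r = 0.3) to 25% (r = 0.5), and by 4% to 49% over the wider assumed range of 0.2 to 0.7. Randomisation keeps an unadjusted comparison unbiased in expectation, so the loss is one of precision unless baseline is averaged into the arm effect.

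The article calls the secondary analyses exploratory. The primary test and the 240 evaluable (268 enrolled) patients do not change. This is a low-severity improvement.

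**What to change.** 1. Mark the laboratory at the day -7 to -2 visit in Table 1, preferably in a row separate from adverse events and device failure. Enter the routine pre-operative ALT, AST, GGT, eGFR, CRP and leukocyte values in the eCRF, and use them as the reference for change and shift tables. If the full plan already records them, correct the table only.
2. State that HHS and EQ-5D-5L are modelled at the postoperative visits with the pre-operative score as a covariate, plus visit and arm-by-visit terms. An equivalent option is to keep baseline as a response with its mean constrained equal between arms. In either case, say that it is not averaged into the arm effect.

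**Cost.** Item 1 needs a few eCRF fields. Trial status reports the first patient treated on 25 June 2025, so values for patients already treated would have to be retrieved from records. It assumes that routine pre-operative bloods exist, which the reference to standard clinical visits suggests but does not prove. Item 2 is a sentence of analysis wording and needs no new data.
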